**Fig. 3 Fig3:**
[figure not shown]
Calculation of AUC and TWA for intraoperative hypotension

Secondary outcome parameter are:

Composite endpoint: Occurrence of AKI according to KDIGO criteria during the hospital stay or until postoperative day 7and MINS: Defined as increased troponin levels that exceed the 99th percentile of the upper reference limit of the assay after measured directly postoperative, 1^st^ and 7^th^ postoperative day or day of discharge, whatever comes first.Incidence of delirium measured directly postoperative and on the 1^st^ postoperative day by the 3D-CAM Test [15]

Furthermore, intraoperative data, such as anesthesia and surgery time, volume of intravenous fluids (crystalloids, colloids, blood products, and autologous blood), blood loss, transfusion rate, type and dosage of vasopressors, and type and dosage of inotropic medication used during the procedure, were documented.

Finally, the length of hospital and ICU stay and hospital mortality were analyzed.

In addition to the predefined parameters, we will also retrospectively analyze variables related to overtreatment. In particular, we will calculate the area above threshold (AAT), defined as the cumulative time–pressure product with a mean arterial pressure above a threshold of 100 mmHg. This parameter will allow us to assess the extent of potential overtreatment in the intervention group compared to the control group.

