**Methods/design:**

This monocentric, randomized, prospective interventional trial will be conducted at the University Hospital Giessen. The study will include patients aged 45 years and older undergoing major orthopedic or trauma surgeries. Participants will be randomized into two groups: an intervention group receiving hemodynamic management using the ClearSight system in combination with a HPI-based treatment algorithm and a control group receiving standard care. The patients from the standard group also receive continuous cardiac output monitoring; however, this will be blinded to the anesthesiologist, to ensure the comparability of the measured hemodynamic parameters. The primary endpoint is the incidence, duration and severity of IOH, which is defined as MAP < 65 mmHg for at least one minute and which is calculated as the area under MAP < 65 mmHg and the time-weighted average (TWA) of MAP < 65 mmHg. Secondary endpoints include the occurrence of postoperative AKI (measured by KDIGO criteria), MINS (measured by high-sensitivity troponin I assays), and postoperative delirium. The study aims to recruit 150 patients, accounting for potential dropouts, to provide sufficient power to detect differences in the primary and secondary endpoints.

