### Study population

The study will include patients aged 45 years and older undergoing major orthopedic or trauma surgery, such as reconstructive surgery of the pelvis (e.g., stabilization of fractures), total hip or knee arthroplasty, surgery of the proximal femur (e.g., stabilization of fractures), and surgery of the spine in a supine position. A further inclusion criterion is a planned anesthesia time of > 90 min in general anesthesia. Exclusion criteria include invasive blood pressure monitoring, participation in another interventional study, pregnancy and nursing mothers, surgery without controlled mechanical ventilation, patients with ASA I or IV, preexisting arterial fibrillation and known allergy against gelatine.

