### Preoperative management

Patients are recruited before surgery after checking inclusion and exclusion criteria by the dedicated study team. Informed consent is obtained at this time from a study team member. Patients will be randomized 1:1 to the two groups after achieving the patient’s informed consent. Randomization will be performed using computer-generated random numbers and will be performed by the study team. Further, the following basic characteristics are obtained:Age, sex, height, weight, ASA scorePre-existing conditions (hypertension, coronary heart disease with and without history of myocardial infarction, peripheral arterial disease, renal failure, chronic obstructive pulmonary disease, diabetes)Previous major surgeriesCurrent prescription of medicationFurthermore, the following laboratory results will be gained:Blood cell countGlobal coagulatory function (internationalized ratio, thromboplastin time, fibrinogen levels)Parameters of renal function (creatinine, urea,)Parameters of cardiac function (troponin I, creatinine kinase, myoglobin, nt brain natriuretic peptide)Inflammatory Parameters (C-Reactive Protein, Procalcitonin)

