##### Data collection

Data will be collected by the study team preoperatively, intraoperatively, and at multiple time points postoperatively (directly postoperative at the recovery room, 1 postoperative day, 7 postoperative days, or day of discharge, whichever comes first) (Fig. 2). The data collection includes the baseline patients’ characteristics, including blood pressure measurements, renal function markers, and cardiac biomarkers as mentioned before. The intraoperative data will be collected from the HemoSphere monitor, which will collect all hemodynamic data every 20 s, and the electronic patient data management system (NarkoData Version 4.17.12.23066, IMESO, Gießen, Germany). All data will be collected in an electronic database on the university hospital server and will be only available for the study team members.

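### MINS is defined by a postoperative troponin cut-off alone, so a raised value that was already present before surgery, and has not changed, counts as an event

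*Protocol article*

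**What the plan says.** The secondary outcome list in the Outcome section of the protocol article has this criterion: "MINS: Defined as increased troponin levels that exceed the 99th percentile of the upper reference limit of the assay". The samples named are those taken directly after surgery, on day 1, and on day 7 or at discharge. The abstract adds the assay: "MINS (measured by high-sensitivity troponin I assays". MINS is listed together with AKI: "Composite endpoint: Occurrence of AKI according to KDIGO criteria during the hospital stay or until postoperative day" 7, followed by MINS in the same run-on item.

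The preoperative panel (Preoperative management) includes "Parameters of cardiac function (troponin I, creatinine kinase, myoglobin, nt brain natriuretic peptide". The Data collection section confirms that baseline data cover "renal function markers, and cardiac biomarkers as mentioned before". The exclusion list (Study population) ends with "patients with ASA I or IV, preexisting arterial fibrillation and known allergy against gelatine"; nothing in that list refers to raised troponin. Among the pre-existing conditions recorded are "coronary heart disease with and without history of myocardial infarction, peripheral arterial disease, renal failure". The Statistical analysis section compares categorical variables by Fisher's exact test and states no adjustment for baseline.

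**The concern.** The secondary hypothesis is that guided haemodynamic therapy reduces postoperative myocardial injury. An elevation that exists before anaesthesia starts cannot be prevented by intraoperative management. If it stays above the limit, the stated rule still records it as an event, in either arm.

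Such patients are plausible here. The trial enrols people aged 45 and older, includes fracture surgery, expects some patients with coronary disease or renal failure, and uses a high-sensitivity assay. Counting them would:

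- raise the reported MINS rate, and the composite rate if either component suffices;
- pull the relative effect towards 1 and lower power;
- count towards the planned subgroup analysis of patients with secondary endpoints, which is to be done if there are enough of them, and place patients without new injury in that subgroup.

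**Working it through.** **Reading check.** Four parts of the article decide the point.

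1. Definition (Outcome): one operational criterion, above the 99th percentile, applied to postoperative samples. There is no rise and no reference value.
2. Baseline (Preoperative management, Data collection): troponin I is available before surgery.
3. Eligibility (Study population): no exclusion for raised troponin.
4. Analysis (Statistical analysis): Fisher's exact test on the event as defined, so the baseline value does not enter there either.

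A patient above the limit before surgery and unchanged afterwards therefore meets the definition.

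**Size.** The article gives no MINS rate, no share of patients with raised preoperative troponin and no power for MINS, so it has no figure to reproduce. Everything below is illustration.

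Assumptions: new MINS p = 10% (control) and 5% (intervention), independent of baseline status; a share q of patients is above the limit before surgery and stays there.

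- Observed rate = q + (1 − q)p
- Share of counted events that are not new = q(1 − p) / observed rate

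For q = 5%, the control rate is 0.05 + 0.95 × 0.10 = 14.5% and the intervention rate is 0.05 + 0.95 × 0.05 = 9.75%. The share not new in the control arm is 0.05 × 0.90 / 0.145 = 31%.

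| q | Control | Intervention | RR | Risk difference (points) | Not new, control | Not new, intervention |
|---|---|---|---|---|---|---|
| 0% | 10.0% | 5.0% | 0.50 | 5.0 | 0% | 0% |
| 5% | 14.5% | 9.75% | 0.67 | 4.75 | 31% | 49% |
| 10% | 19.0% | 14.5% | 0.76 | 4.5 | 47% | 66% |
| 20% | 28.0% | 24.0% | 0.86 | 4.0 | 64% | 79% |

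Dividing q itself by the observed rate would overstate the last two columns (5/14.5 = 34%, 20/24 = 83%), because some patients with a raised baseline also sustain new injury.

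If q were only 1%, the rates would be 10.9% and 5.95%, with RR 0.55 and a difference of 4.95 points, which is a slight effect.

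**Power at 75 per arm** (two-sided 0.05, normal approximation). With 10% versus 5% and q = 0, the standard error is √[(0.10 × 0.90 + 0.05 × 0.95)/75] = 0.0428. Then 0.05/0.0428 − 1.96 = −0.79, which is about 21% power. With q = 20%, the standard error is √[(0.28 × 0.72 + 0.24 × 0.76)/75] = 0.0716. Then 0.04/0.0716 − 1.96 = −1.40, about 8%. With larger assumed rates of 20% versus 10%, power falls from 40% to 31%, 25% and 18% at q = 5%, 10% and 20%.

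**The case against.** **The definition may intend a rise.** It speaks of increased levels, the outcome is named as injury after surgery, and a baseline sample is drawn. The sentence is also garbled, and the full protocol is not shown. This has some force as to intent. But the only criterion attached to the word is a fixed percentile. If a rise was meant, neither its size nor its reference value is given. The article states a rule, and that rule misclassifies these patients; this is more than detail left to another document.

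**The size is assumed.** This stands. The prevalence cannot be taken from the documents, and nothing in them supports 20% in particular. The exclusions of ASA IV, fibrillation and invasive pressure monitoring may remove some of the likeliest patients.

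**The risk ratio makes it look worse than it is.** Partly right. The plan names no effect measure, and on the risk-difference scale the shrinkage is 5% to 20% (0.25/5 to 1.0/5).

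**The trial was not sized for MINS.** Also right. The Limitations section says power may be lacking for AKI and MINS. Under the assumed 10% versus 5%, power is low with either definition.

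Two stronger readings do not hold. A reader might infer that the definition favours the device. Randomisation balances pre-existing elevations on average, so dilution is expected and not bias, although chance imbalance is possible at 75 per arm. A reader might also take the composite to require both AKI and MINS. The wording occurs in a run-on list, while the abstract and the secondary hypotheses treat the two as separate outcomes. That makes it a minor point of wording.

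**Conclusion.** The concern holds as a misclassification in a secondary endpoint. Read as written, the definition counts an unchanged pre-existing troponin elevation as postoperative myocardial injury, although the value needed to tell the two apart is collected. That conclusion rests on the text and not on any assumed rate.

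The expected consequence is inflated MINS and composite rates and a diluted contrast, in a comparison that already has limited power. The illustrated RR of 0.67 to 0.86 in place of 0.50 depends on three assumptions: new MINS of 10% versus 5%, 5% to 20% of patients already elevated, and elevations that persist after surgery. With few such patients the effect would be slight. The primary endpoint is not affected.

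**What to change.** Before analysis, define MINS as a postoperative troponin I above the assay's 99th percentile together with a pre-specified rise over the patient's own preoperative value. State the relative or absolute change that applies to patients already above the limit. Report MINS and AKI separately as well as in the composite. As a minor clarification, word the composite as AKI and/or MINS, so that one component suffices.

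The cost is a sentence or two. No new sample or visit is needed, since preoperative troponin I is already in the baseline panel. The downside is a lower MINS count.

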### Sample size calculation

The study aims to enroll 150 patients to ensure adequate power. The aim of the study is to show the impact of non-invasive cardiac output monitoring on the incidence of IOH in a cohort of trauma and orthopedic surgery. Sample size calculation was performed with regard to a study by Maheshwari et al. who investigated the effect of HPI on the prevention of hypotension [16]. This study was chosen because the primary endpoint, respectively the definition of hypotension (MAP < 65 mmHg), was identical to our study, and they investigated also non-cardiac surgical patients. In this study, the mean area under the curve of MAP ≤ 65 mmHg of patients without hemodynamic management accounted for 34.2 mmHg min (8.5–112.7) compared to 32.7 mmHg min (6.3–102) in patients with hemodynamic measurement. Aiming for an alpha of 0.05 and power of 0.95, the sample size calculation resulted in 66 patients per study group (total 132 patients, based on the use of the Wilcoxon test). In order to address potential dropouts (estimated drop-out rate 10–20%), we chose to increase the patient numbers to 75 patients in each study group. In addition, if the number of patients with secondary endpoints is sufficient, a subgroup analysis of these patients is planned.

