### Statistical analysis

Next to the target parameters, data of the hemodynamic and respiratory function will be achieved as well as of the anesthetic and hemodynamic management. Furthermore, general characteristics such as age, gender, body mass index, as well as pre-existing conditions and prescriptions will be assessed.

For the target variables, the results will be investigated and analyzed descriptively (e.g., checked for distribution). Metric characteristics (mean and standard deviation). as well as median and interquartile difference, and achieved frequencies (with a percentage specification) will be determined. As part of the exploratory analysis, the structural equilibrium (homogeneity) of the treatment groups will also be checked.

The distribution of parameters will be assessed using the Shapiro test, and *T *test and Wilcoxon test will be utilized accordingly for calculating group differences, considering a two-tailed value of *p* < 0.05 to be statistically significant. Categorial variables will be tested for statistically significant differences by Fisher’s exact test.

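### The planning figures quoted for the sample size (34.2 versus 32.7 mmHg·min) cannot give 66 patients per group at 95% power, and the effect that would is not stated

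*Protocol article*

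**What the plan says.** The Sample size calculation section of the protocol article takes its figures from one cited study, "who investigated the effect of HPI on the prevention of hypotension [16". It calls the area under the curve a mean and reports that "patients without hemodynamic management accounted for 34.2 mmHg min (8.5–112.7" mmHg·min, "compared to 32.7 mmHg min (6.3–102) in patients with hemodynamic measurement". The brackets are not defined. It continues "Aiming for an alpha of 0.05 and power of 0.95" and concludes that "the sample size calculation resulted in 66 patients per study group (total 132 patients, based on the use of the Wilcoxon test". Enrolment is then raised for dropout: "In order to address potential dropouts (estimated drop-out rate 10–20%), we chose to increase the patient numbers to 75 patients in each study group".

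Allocation is equal (Preoperative management: "Patients will be randomized 1:1 to the two groups"). Sidedness appears only under Statistical analysis: "considering a two-tailed value of *p* < 0.05 to be statistically significant". No target reduction, standard deviation or other effect size is given anywhere in the article. The Limitations section relies on the calculation when it describes the 150 patients as sized for the primary outcome. The Outcome section measures severity by the time-weighted average (TWA), which is the area divided by anaesthesia duration.

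**The concern.** The two planning values differ by 34.2 − 32.7 = 1.5 mmHg·min, or 4.4% of the control value, while the brackets around them are 104.2 and 95.7 mmHg·min wide. A difference that small against a spread that large cannot be detected with 95% power by a two-group test of 66 per group. Yet the text presents 66 as the output of a calculation on these inputs.

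Power of 95% is the main claim made for the design. If it does not follow from what is written, a reader cannot tell what effect the trial was built to find. A non-significant result then could not be interpreted against a known target.

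**Working it through.** **Inputs.** Sample size calculation: 34.2 (8.5–112.7) and 32.7 (6.3–102), alpha 0.05, power 0.95, Wilcoxon test, 66 per group. Statistical analysis: two-tailed. Preoperative management: 1:1. The spread is an assumption, because the brackets are undefined; several readings are tried.

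**Formulas.** With 1.960 + 1.645 = 3.605 (squared, 12.995) and Wilcoxon efficiency 3/π = 0.955:
- n per group = 2 × 12.995 / (0.955 × d²), where d is the difference divided by the SD
- power = Φ(d√(0.955n/2) − 1.960) + Φ(−d√(0.955n/2) − 1.960)
- SD per arm = bracket width / k, pooled over arms. On the log scale the width is ln(upper/lower) and the difference is ln(34.2/32.7) = 0.0449.

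**Trying to reproduce 66.** With brackets read as quartiles (k = 1.349), the SDs are 104.2/1.349 = 77.2 and 95.7/1.349 = 70.9, pooled 74.2. Then d = 1.5/74.2 = 0.0202 and n ≈ 66,500 per group, not 66. The other readings, with power at 66 per group:

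| Bracket read as | k | Raw SD | Raw d | Raw n | Raw power | Log SD | Log d | Log n | Log power |
|---|---|---|---|---|---|---|---|---|---|
| quartiles | 1.349 | 74.2 | 0.020 | 66,500 | 5.1% | 1.99 | 0.023 | 53,700 | 5.2% |
| 10–90% range | 2.563 | 39.0 | 0.038 | 18,400 | 5.5% | 1.05 | 0.043 | 14,900 | 5.7% |
| 95% range | 3.92 | 25.5 | 0.059 | 7,900 | 6.3% | 0.685 | 0.065 | 6,400 | 6.6% |
| minimum–maximum (range/6) | 6 | 16.7 | 0.090 | 3,360 | 8.0% | 0.448 | 0.100 | 2,710 | 8.7% |

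**Distributions matched to all three values per arm** (quartile reading). A split log-normal gives a probability of 0.524 that a control value exceeds an intervention value. Noether's formula gives a total of 12.995 / (3 × 0.0244²) ≈ 7,270, or about 3,600 per group. A piecewise-linear distribution gives about 3,800 per group. Simulated Mann–Whitney power at 66 per group is 7.3% and 7.6% (20,000 runs each).

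**Variants that favour the plan.**
- Taking the log midpoint of the quartiles as the location gives about 9% two-sided power and about 2,700 per group. One-sided it gives at most 14% and still more than 2,100 per group.
- Using 75 per group, with no dropout, leaves two-sided power at about 5–9%.
- Power rises well above this only if the quoted central values are set aside, the log midpoints of the brackets become the effect (difference 0.1996) and the brackets are read as minimum–maximum. Then d = 0.1996/0.448 = 0.446 and n = 2 × 12.995 / (0.955 × 0.446²) ≈ 137 per group. That is no longer a calculation on 34.2 versus 32.7, and it still does not give 66.

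**Working backwards from 66.** d = 3.605 × √(2/(66 × 0.955)) = 0.642, or about 0.65 with the t correction. As a probability of a lower value under the intervention, this is 0.5 + 3.605/√(3 × 132) = 0.68. With a difference of 1.5, the SD would have to be 1.5/0.642 ≈ 2.3 mmHg·min, which cannot fit brackets about 96–104 wide.

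**What that shift means as a reduction depends on the bracket reading** (log scale, 66 per group):
- Quartiles: exp(−0.642 × 1.99) = 0.28, a 72% reduction (34.2 to about 9.5). A halving has d = 0.693/1.99 = 0.348 and about 50% power.
- 10–90% range: a 49% reduction. A halving has about 96% power.
- 95% range: a 36% reduction. A halving has over 99% power.

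**The case against.** The best defence is that the section ties its calculation to the cited study without saying that the 1.5 mmHg·min difference is the target. The quoted values may have served only as a reference level or spread, with the effect set out in the full protocol, which is not shown. That is possible, and it limits the conclusion. A reader might infer that the trial's real power is 5–9%; the article does not support this, because the effect actually planned for is unknown. The defence does not rescue the text, which states inputs and a result that cannot come from them.

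A reader might also infer that the design can detect only a very large reduction, such as 72%. That holds only if the brackets are quartiles. The asymmetry (25.7 below and 78.5 above the control value) makes medians with quartiles the likely reading and the label of mean doubtful, but the article does not settle it. Under a 10–90% reading a halving would be well powered. The raw-scale equivalent under quartiles, 0.642 × 74.2 ≈ 48 mmHg·min, exceeds the control value of 34.2; this mainly shows that a normal model does not suit these data.

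Finally, every figure here concerns the area in another study. The spread of TWA in this trial is not given, and the incidence part of the primary outcome is not covered by either calculation.

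**Conclusion.** The point holds as a sample size that cannot be reproduced from its stated inputs. With 34.2 versus 32.7 as the effect, two-sided power at 66 per group is about 5–9%, and 95% power would need roughly 2,700 to 66,500 per group. This rests on two-sided alpha 0.05, equal groups and Wilcoxon efficiency 3/π. It does not depend on which of the bracket readings tried is right.

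The 66 requires a standardised shift of about 0.64–0.65, and nothing in the article states or supports one. The 72% detectable reduction and the 50% power for a halving are conditional on the quartile reading and should not be taken as properties of the design. The point should be corrected before the 95% power claim is relied on.

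**What to change.** Keep the 150 patients and rewrite the derivation:

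- Delete the claim that 34.2 versus 32.7 yields 66 per group.
- State and justify the effect, spread, distribution and sidedness actually used, for the outcome that will be tested (TWA, not only the area).
- If these cannot be recovered, say that 66 per group gives 95% power only for a standardised shift of about 0.65 (probability of a lower value about 0.68). That describes what the size supports; it is not evidence that such an effect is plausible.
- Give power for smaller reductions, with the assumed spread shown beside each figure.
- Check the quoted summaries against their source and label them for what they are; medians with quartiles seems likely.
- Bring the power statements in the Abstract and Limitations into line.

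The cost is rewording, with no extra patients. The downside is that the stated power becomes less favourable.

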### Limitations

The study may face several limitations that could influence the interpretation of its future results. As a monocentric trial, the findings will reflect the practices and patient populations of a single institution, potentially limiting their generalizability. A multicenter approach could provide more comprehensive insights. Additionally, while the chosen sample size of 150 patients is calculated to detect primary outcomes, it may lack the statistical power to observe rarer complications, such as reductions in AKI or MINS. The study design includes blinding advanced hemodynamic data from the control group while providing detailed monitoring for the intervention group, which may introduce biases in clinical management due to the differing availability of information. Moreover, the intervention group in our study combines continuous non-invasive monitoring with goal-directed therapy (targeting CI and SV) and the HPI early-warning alarm; therefore, observed effects should be interpreted as the result of this multimodal strategy rather than HPI alone. Furthermore, the outcomes will depend on the ClearSight system’s accuracy and functionality, meaning that any technical inconsistencies could affect the results.

The focus on short-term outcomes may overlook the impact on long-term recovery and organ function, including sustained renal and cardiac health. Finally, the variability in patient characteristics, due to the inclusion of different types of orthopedic and trauma surgeries, could add complexity when attributing results directly to the intervention.

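### Enrolling 150 covers dropout only up to 12% of the stated 10–20%, and the abstract's claim of sufficient power for the secondary endpoints has no calculation behind it

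*Protocol article*

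**What the plan says.** The Sample size calculation section of the protocol article sizes the trial on one quantity, the area under the curve of MAP below 65 mmHg. It reports that "the sample size calculation resulted in 66 patients per study group (total 132 patients, based on the use of the Wilcoxon test"). It then gives an expected dropout of 10–20% and says that, to address it, "we chose to increase the patient numbers to 75 patients in each study group", 150 in total. It gives no event rate, effect or power for AKI, MINS or delirium. It adds only that patients with secondary endpoints will be analysed as a subgroup if there are enough of them.

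The abstract (Methods/design) says that 150 patients, with dropouts accounted for, are recruited "to provide sufficient power to detect differences in the primary and secondary endpoints".

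The Limitations section says of the same 150 that "it may lack the statistical power to observe rarer complications, such as reductions in AKI or MINS".

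**The concern.** Two statements about what 150 patients deliver do not fit the article's own figures.

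- **Dropout margin.** The requirement, the expected loss and the enrolled number are all stated, and the third does not follow from the first two over most of the range. If losses run above 12%, the trial falls below the size it says it needs.
- **Secondary endpoints.** The abstract makes a positive power claim that the body does not support and partly withdraws. AKI, MINS and delirium carry formal directional hypotheses (Secondary hypotheses section). A non-significant result on any of them, read beside the abstract, could be taken as an adequate test that found nothing.

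**Working it through.** **Inputs from the article.** 66 evaluable per group (132 in total), dropout 10–20%, 75 enrolled per group (Sample size calculation). Design values: "Aiming for an alpha of 0.05 and power of 0.95". Allocation: "Patients will be randomized 1:1 to the two groups". Tests are made "considering a two-tailed value of" p < 0.05, with Fisher's exact test for categorical variables (Statistical analysis).

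**1. Where 75 comes from.** Required enrolment is n/(1 − d).

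| Dropout d | 66/(1 − d) | Per group | Left of 75 | Left of 150 |
|---|---|---|---|---|
| 10% | 73.3 | 74 | 67.5 | 135 |
| 12% | 75.0 | 75 | 66 | 132 |
| 15% | 77.6 | 78 | 63.75 | 127.5 |
| 20% | 82.5 | 83 | 60 | 120 |

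The figure of 75 is reproduced exactly at d = 1 − 66/75 = 12.0%. At 20% the requirement is 83 per group (166), or 132/0.80 = 165 worked on the total. Even the too-lenient formula n × (1 + d) gives 66 × 1.20 = 79.2, so 80 per group.

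**2. What the shortfall costs, if 66 gives 95% power.** The standardised difference that 66 per group detects with 95% power (two-sided 0.05, normal approximation) is (1.960 + 1.645) × √(2/66) = 0.628. With 60 per group, power is Φ(0.628 × √(60/2) − 1.960) = Φ(1.477) ≈ 0.930. The loss is about 2 points.

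**3. Why that figure is conditional.** The article's stated effect is that the area "accounted for 34.2 mmHg min (8.5–112.7) compared to 32.7 mmHg min (6.3–102"), a difference of 1.5 mmHg min. It states no SD. If the brackets are interquartile ranges (an assumption), the SDs are (112.7 − 8.5)/1.349 = 77.2 and (102 − 6.3)/1.349 = 70.9, pooled about 74. The standardised difference is then 1.5/74 ≈ 0.02, and 95% power needs about 63,500 per group. Treating the brackets as full ranges (SD about 17–26) still gives about 3,500–7,800. So 66 per group does not follow from the stated inputs. The 0.628 above is solved back from 66 and is not an effect that the article states.

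**4. Secondary endpoints.** The article gives no rates, so the control risks below are assumptions. Exact power of the two-sided Fisher test for a halving of risk:

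| Control risk → intervention risk | 60 per group | 66 per group | 75 per group |
|---|---|---|---|
| 10% → 5% | 9% | 10% | 13% |
| 20% → 10% | 25% | 28% | 32% |
| 25% → 12.5% | 33% | 38% | 42% |
| 30% → 15% | 42% | 47% | 53% |
| 40% → 20% | 60% | 65% | 71% |

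For a 25% relative reduction, power at 66–75 per group is at most about 20% over the same risks. For scale, 80% power by the normal approximation needs 435 per group for 10% against 5%, 199 for 20% against 10%, and 152 for 25% against 12.5%.

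**The case against.** **The dropout gap is immaterial.** 75 per group covers the lower end of the stated range, and the article says the increase addresses dropout, not that it fully offsets 20%. At the worst stated loss power would fall only from 95% to about 93%. This stands: it is a correction to a sentence. A reader might infer that the primary comparison is undermined or that more patients must be recruited. The documents do not support that on dropout grounds.

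**The Limitations section already gives the caution.** It does for AKI and MINS, and the Sample size calculation section ties 150 to the primary measure alone. A reader might infer that the Limitations flatly contradict the abstract. They do not quite: the wording is hedged, concerns rarer complications, and does not name delirium. But the abstract's claim is unqualified, no calculation supports it for any secondary endpoint, and the abstract is what most readers will see.

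**The secondary power figures rest on assumed risks.** They do. The Outcome section lists AKI and MINS under a composite endpoint, whose rate may exceed that of either component. This is why the range runs to 40%, where power is highest but still 65–71%. Control risks above 40%, or reductions larger than a halving, were not examined.

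**Conclusion.** The point holds as two wording errors of unequal weight.

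The dropout statement is wrong as arithmetic: 150 allows for 12.0% loss and leaves 12 patients too few at 20%. The consequence is minor, and both the 12% and the 2-point loss are only as sound as the 66 per group.

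The abstract's power claim matters more. It is unsupported for every secondary endpoint and sits against the Limitations section for AKI and MINS. Under assumed control risks of 10–40% and a halving of risk, power at 66–75 per group is about 10–71%. The exact shortfall cannot be fixed because the article gives no rates.

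Two further inferences are tempting and go too far. One is that the protocol should state 93% power at 20% dropout; that would add a figure resting on an effect the article neither states nor reproduces. The other is that AKI, MINS and delirium must become estimation-only endpoints. Underpowered secondary endpoints may still be tested, and relabelling would conflict with the stated secondary hypotheses and the planned Fisher tests.

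**What to change.** Keep 150 and change three statements.

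1. **Sample size calculation:** say that 75 per group allows for up to 12% dropout, and that 20% dropout would leave 60 per group, below the stated 66. Add no power figure for that case unless the effect size behind the 66 is first stated and reproduced.
2. **Abstract, Methods/design:** delete *and secondary* from the power statement.
3. **Limitations, and the eventual report:** say that the trial is not powered for AKI, MINS or delirium, so a non-significant result there is not evidence of no effect.

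The secondary hypotheses and tests stay as they are. The cost is a few sentences: no extra patients and no change to design or conduct. The stated claims become somewhat less favourable.
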